## Methodology

### Study design

This study will be a prospective equivalence randomized, double-blind controlled trial conducted in the department of surgery at Kampala International University Teaching Hospital (KIU-TH), western Uganda.

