### Sample size determination

The randomized control trial assumes a null hypothesis that the mean postoperative pain scores after hemorrhoidectomy using local anesthesia are not different from that done under saddle block by a clinically relevant amount. Since the primary outcome measure was a continuous variable (i.e., pain level measured using a visual analog scale), the formula for an equivalence design in randomized control trials by Zhong et al. [15] was used.$$\boldsymbol{N}=\mathbf{2}\times {\left\{\frac{{\boldsymbol{Z}}_{\mathbf{1}-\propto}+{\boldsymbol{Z}}_{\mathbf{1}-\boldsymbol{\beta}}}{\boldsymbol{\delta}}\right\}}^{\mathbf{2}}\times {\boldsymbol{S}}^{\mathbf{2}}$$

where

***N***sample size per group

***Z***_***1−α***_standard normal deviate for a two-sided test used in equivalence trials (1.96 for 95% confidence interval)

***δ***clinically admissible margin of equivalence design as a difference

***α***type I error associated with rejecting the null hypothesis when it is true; (0.05) for 95% confidence interval

***β***type II error associated with the alternative hypothesis, assumed to be 0.20 for a statistical power of 80%

**(1−*****β*****)**the probability of rejecting the null hypothesis when it is false, i.e., *Z*_1−*β*_ = 0.845 for statistical power of 80%

***S***^**2**^pooled standard deviation of both comparison groups

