According to a similar randomized control trial that compared open hemorrhoidectomy under local anesthesia versus supine anesthesia at the Korle Bu Teaching Hospital in Ghana [16], the difference in the mean pain scores between the 2 groups was *δ* = 0.73; pooled standard deviation in the mean pain scores *S* = 1.9 (average of 2.356 for local anesthesia and 1.479 for supine anesthesia), an estimated sample size of 104 participants per group, was obtained. Since at the time of the proposed study, nothing was known about the mean pain score following OH under local anesthesia and the real difference in clinical outcome between the two techniques in Uganda, the sample size was adjusted using Slovin’s formula as detailed by Ellen [17] based on the hospital records, Kampala International University Teaching Hospital which registered an average of 33 cases of grade 3 or 4 hemorrhoids in a period of 6 months that corresponded to the intended data collection period; thus, a sample size of 26 participants per group was obtained which was increased to 29 participants in each arm, based on a rate of 10% in each arm to compensate for the loss to follow-up and non-responsiveness found.

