### Trial status

The first case was recruited on 2 December 2021, and as of 7 April 2022, 45 patients were registered out of the required sample size of 58 for this protocol version 3 as of 21 May 2022.

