### Study limitations

Lack of cooperation or withdrawal of consent by some participants during the study will be managed by doing a comprehensive counseling of participants with regard to the participation. The formula produces a ballpark figure to work with and lacks statistical power of obtaining the error of tolerance according to Ryan (2013). No similarity in the price of materials used during the study will be settled by the use of prices from the Joint Medical Store of Uganda to standardize the prices.

The error of tolerance was obtained from a set error margin for a confidence interval of 95 using tables, to increase the power of precision in sample size determination occurrence. Targeted population computation was done from reliable sources of HMIS data based on the Ugandan Ministry of Health for the 3 months for KIU-TH to get the average population per month. The sample size has been adjusted to cater for loss to follow-up.

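### Slovin's formula cuts the equivalence sample size from 104 to 29 per arm without restating power, so the equivalence label has no statistical support at the size actually used

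*Protocol article*

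**What the plan says.** The Study design section sets the aim: "This study will be a prospective equivalence randomized, double-blind controlled trial". The title and the Methods part of the abstract use the same label.

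The Sample size determination section uses an equivalence formula for a continuous pain score. It defines delta as the "clinically admissible margin of equivalence design as a difference", uses 1.96 for 95% confidence, and has beta "assumed to be 0.20 for a statistical power of 80"%. Delta is set at 0.73 and the SD at 1.9, both from a trial in Ghana, and the result is 104 per group.

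The same section then says that the local pain score and the real difference in Uganda were unknown, and adjusts the figure with Slovin's formula. The population used is the hospital's own count, which "registered an average of 33 cases of grade 3 or 4 hemorrhoids in a period of 6 months"; "thus, a sample size of 26 participants per group was obtained which was increased to 29 participants in each arm", the increase being for 10% loss.

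Power, margin and SD are not restated for 29 per arm. Study limitations remarks: "The formula produces a ballpark figure to work with and lacks statistical power". The sentence goes on to refer to the error of tolerance, and nothing in the design or its claims is changed as a result.

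**The concern.** Slovin's formula and finite-population corrections answer a survey question: how many people from a list of known size must be measured to describe that list with a given tolerance. A randomised comparison estimates a treatment difference, and its standard error depends on the outcome SD and the number per arm. The number of patients the hospital happens to see does not enter. Not knowing the local SD or difference is a reason for caution, not for a smaller trial.

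The step also fails on its own terms. The 33 cases are all the patients expected in six months, yet the output is 26 per group, so 52 in total and 58 after inflation, which is more than the population sampled from.

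What is at stake is the conclusion. The Hypothesis section is worded as no significant difference, and the Data processing and analysis plan tests differences at p < 0.05. With an interval this wide, a non-significant result is the likely outcome whether or not the techniques differ by 0.73. Under an equivalence label it could be taken as showing that they are the same.

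**Working it through.** **Inputs.** All are from Sample size determination: margin 0.73, SD 1.9, z = 1.96 and 0.845, 104 then 26 then 29 per arm, population 33, loss 10%. A true difference of zero is an assumption, and the one most favourable to equivalence.

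**1. The plan's own figures**
- N = 2 × ((1.96 + 0.845)/0.73)² × 1.9² = 106.6, so 107. The stated 104 is within 3%; nothing here turns on that gap.
- The route to 26 is not shown. Slovin's 33/(1 + 33e²) gives 30.5 at e = 0.05, 24.8 at e = 0.10 and 26.04 at e = 0.09. A finite-population correction, 104/(1 + 103/33) = 25.2, also rounds up to 26. None of these routes concerns a two-arm comparison.
- 26/0.90 = 28.9, so 29 per arm and 58 in total.

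**2. Precision on the mean VAS score, SD 1.9**

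The standard error is 1.9 × √(2/n), and the half-width is the t quantile times this.

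| Per arm | SE | 95% half-width | 90% half-width |
|---|---|---|---|
| 26 | 0.527 | 2.009 × 0.527 = 1.06 | 1.676 × 0.527 = 0.88 |
| 29 | 0.499 | 2.003 × 0.499 = 1.00 | 1.673 × 0.499 = 0.83 |

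All four exceed 0.73. If the sample SD came out near 1.9, an observed difference of exactly zero would still not place the interval inside ±0.73.

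**3. Power for equivalence within ±0.73**

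This is the probability that the whole interval lies inside the margin, integrated over the sampling distribution of the SD.

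| Per arm | 95% interval | 90% interval |
|---|---|---|
| 26 | 0.002% | 0.21% |
| 29 | 0.006% | 0.55% |
| 104 | 57% | 74% |

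The 104 falls short of 80% here because the plan's formula uses z for 1 − β, whereas two-sided equivalence with a zero difference needs 1 − β/2. With that term, about 143 (95% interval) or 117 (90% interval) evaluable patients per arm would be needed. Taken as a one-term formula, as the plan does, power is about 79% at 104 and 31% at 29. The 31% is also the power of an ordinary two-sided test to detect a true difference of 0.73, so such a test would be non-significant about 69% of the time.

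**4. Sensitivity to the SD, 29 per arm**

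The primary outcome is the AUC of VAS, for which no SD or margin is given. As an illustration, take the mean of four scores, each with SD 1.9 and common correlation r. Its SD is 1.9 × √((1 + 3r)/4), which is 1.20 at r = 0.2 and 1.50 at r = 0.5.

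| SD | 95% half-width | Power, 95% interval | Power, 90% interval |
|---|---|---|---|
| 1.20 | 0.63 | 25% | 48% |
| 1.479 (smaller SD cited, both arms) | 0.78 | 2.4% | 17% |
| 1.50 | 0.79 | 2% | 15% |

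No row approaches 80%.

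**The case against.** Several stronger readings are tempting and do not hold.

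- **That the plan claims 80% power for 29 per arm.** It does not. The 80% is an input to the 104 and is legitimate there. What can be said is that it is the only power figure given and that nothing replaces it after the cut.
- **That the trial has no chance of showing equivalence on its primary outcome.** The power below 1% is for a mean VAS score with SD 1.9. A summary over repeated scores may vary less, and power could then reach the 2–48% shown above. An AUC weighted by time is dominated by the span from 6 h to day 7 and would gain less.
- **That accrual contradicts the count of 33.** Trial status reports that "as of 7 April 2022, 45 patients were registered out of the required sample size of 58". A historical average and later trial registration are different quantities; the comparison shows a poor forecast, not a contradiction.
- **That Study limitations already concedes the point.** The remark concerns the formula and its tolerance error. It does not say that equivalence is out of reach. Nor does it excuse the gap, since no claim is altered.
- **That the claim of level 1 evidence in Study strengths is a claim of equivalence.** It is attached to the trial being randomised.

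It is fair to add that 58 may be all that one hospital can recruit in six months. That is a sound reason for the size. It is not a statistical derivation of it.

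**Conclusion.** The point stands. The reduction from 104 to 29 per arm has no statistical basis for a two-arm comparison, power at the final size is not stated, and the equivalence label is unsupported. On the plan's own inputs (mean VAS, SD 1.9, margin 0.73, true difference zero), the 95% interval is about ±1.00 and equivalence power is below 1%. With an assumed SD of 1.2 to 1.5 for the AUC on the VAS scale, power is about 2–25% with a 95% interval or 15–48% with a 90% interval. Any real difference between the techniques lowers these figures. The exact route to 26 remains unknown, but the conclusion does not depend on it.

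**What to change.** - Keep 58 as a feasibility size, justified by expected recruitment, and delete the Slovin step as a statistical justification.
- State that 80% power applied only to the 104 per group. Give the figures for 29 per arm, labelled as mean-VAS figures: 95% interval about ±1.00, 90% about ±0.83, equivalence power below 1% at SD 1.9.
- Present the trial as an estimation or pilot comparison that reports the confidence interval against 0.73. State that a non-significant difference will not be read as equivalence, and remove the unqualified equivalence claim from the title, abstract and Study design.
- Do not widen the margin to fit the sample. An interim analysis of the primary outcome was done on 10 March 2022 and 45 of 58 patients were registered by 7 April 2022, so a margin worked back from the sample size now would not be credible.

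The cost is rewording only, with no extra patients. The downside is that the stated power and the design claim become less favourable.

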### Study variables

#### Primary outcome variable

The occurrence of pain following open hemorrhoidectomy will be determined in both groups using the area under the curve (AUC) for visual analog scale (VAS). The VAS will be used in an interval of 2, 4, and 6 h and 7 days postoperatively (the lower end of the scale labeled “0” means no pain while the upper end of the scale “10” signifies the worst imaginable pain).

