### Data processing and analysis plan

Data will be statistically analyzed using IBM Statistics SPSS for Windows 23.0. The primary outcome will analyze all randomized patients (on an intent-to-treat (ITT) basis) and per-protocol (PP) population. The mean pain scores at rest and their standard deviations will be computed and compared using one-way ANOVA tests. VAS will be stratified as ordinal (0 as no pain, 1–3 as mild, 4–6 as moderate, and 7–10 as severe); the significance of the difference in the mean scores between local and saddle groups will be determined by the Kruskall-Wallis (*H*) test at 95% confidence interval, regarding *p* < 0.05 as statistically significant; furthermore, the mean pain scores will be analyzed for significant differences in the area under the curve (AUC) for VAS (2-sample *t*-test). The mean operative time and standard deviation will be computed for each technique of open hemorrhoidectomy. Cross tabulation will be performed between the two open hemorrhoidectomy techniques for categorical cost-effective analysis. The difference in the means will be compared using the *t*-test and their corresponding two-tailed p-value, regarding *p* < 0.05 as statistically significant.

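### The named primary outcome (AUC of VAS) has no stated equivalence criterion: the 0.73 margin is set for a mean score, three pain analyses are unranked, and none uses the margin

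*Protocol article*

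**What the plan says.** In the Protocol article, the section Primary outcome variable says that pain "will be determined in both groups using the area under the curve (AUC) for visual analog scale (VAS". It gives the readings as follows: "The VAS will be used in an interval of 2, 4, and 6 h and 7 days postoperatively", on a scale from 0 to 10. It gives no unit for the area and does not say whether the area is divided by time.

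The section Sample size determination works with another quantity. Its hypothesis is that "the mean postoperative pain scores after hemorrhoidectomy using local anesthesia are not different from that done under saddle block by a clinically relevant amount". It defines δ as the "clinically admissible margin of equivalence design as a difference" and takes its value from an earlier trial in Ghana, where "the difference in the mean pain scores between the 2 groups was" 0.73, with a pooled SD of 1.9. Both figures are VAS points on a mean score.

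The section Data processing and analysis plan names three analyses of pain:

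- "The mean pain scores at rest and their standard deviations will be computed and compared using one-way ANOVA tests";
- a grouping of the scores into four ordered grades, from none to severe, with the groups compared by a Kruskal-Wallis test;
- the AUC, brought in as a further analysis and compared by a two-sample t-test.

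The only criterion given there is significance of a difference at p < 0.05. No analysis is marked as decisive, and δ does not appear.

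**The concern.** An equivalence conclusion needs three things that fit together: one measure, a margin in that measure's units, and a rule that sets the estimate and its interval against the margin. Here the measure is an AUC, the margin belongs to a mean score, and the rule is a test of difference.

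The forms weight the four readings very differently, so they can disagree about the same patients. With no form marked as decisive, equivalence could be claimed on whichever one shows the arms most alike. Because every test looks for a difference, a non-significant p-value could also be taken as equivalence, which it does not establish.

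**Working it through.** **Inputs.** Readings at 2, 4, 6 and 168 h (7 days) come from Primary outcome variable. δ = 0.73, S = 1.9, and normal deviates of 1.96 and 0.845 come from Sample size determination. Two assumptions are mine, because the article states neither: the AUC is trapezoidal over all four readings, and the mean score is the unweighted average of the four.

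**1. Which quantity the margin belongs to.** The article's formula gives N = 2 × ((1.96 + 0.845)/0.73)² × 1.9² = 2 × 14.765 × 3.61 = 106.6, so 107 per group. The article reports 104, a gap of 3 (about 3%). The margin and SD thus enter as mean-score figures, and no step of the sizing uses an AUC.

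**2. The margin carried to an AUC.** From 2 h to 168 h the span is 166 h. A constant 0.73-point difference is 0.73 × 166 = 121.2 point-hours. Over 2 to 6 h only, it is 0.73 × 4 = 2.92 point-hours. An AUC margin therefore depends on the window and the scaling, and the article fixes no scaling.

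**3. Weights.**

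| Reading | Trapezoid weight (h) | Share of 166 h |
|---|---|---|
| 2 h | 1 | 0.6% |
| 4 h | 1 + 1 = 2 | 1.2% |
| 6 h | 1 + 81 = 82 | 49.4% |
| 7 days | 81 | 48.8% |

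The 6 h and day-7 readings carry (82 + 81)/166 = 98% of the AUC. In an unweighted mean each reading carries 25%.

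**4. The same data in two forms, set against 0.73 as point differences.**

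- A 2-point difference at 2 h and 4 h only. Unweighted mean: (2 + 2 + 0 + 0)/4 = 1.00, outside. Time-averaged AUC: (1 × 2 + 2 × 2)/166 = 6/166 = 0.036, inside.
- A 1-point difference at 6 h and day 7 only. Unweighted mean: (0 + 0 + 1 + 1)/4 = 0.50, inside. Time-averaged AUC: (82 + 81)/166 = 0.98, outside.

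The disagreement runs in both directions.

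**5. The SD does not carry over either.** Suppose each reading has SD 1.9 and any two readings have correlation ρ (assumed, 0 to 0.7). The squared shares sum to 0.482, so the SD of the time-averaged AUC is 1.9 × √(0.482 + ρ × 0.518).

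- ρ = 0: SD = 1.32.
- ρ = 0.7: SD = 1.75.

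With 2 × (2.805/0.73)² = 29.53, the article's formula gives 29.53 × 1.319² = 51.4 and 29.53 × 1.746² = 90.0. That is about 52 to 90 per group, against 107 for a score with SD 1.9. The range only shows that 1.9 is not the SD of this measure. It is not a proposed sample size.

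**6. The decision rule.** ANOVA, Kruskal-Wallis and the t-test each ask whether the arms differ. None sets an interval against 0.73, on any form of the outcome.

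**The case against.** The best defence is that the article does name one primary measure, the AUC, and gives it a matching t-test. The mean scores and grades can be read as supportive. Measurement at rest adds a condition and contradicts nothing. The ranking of analyses and the scaling of an AUC are commonly left to a full protocol or SAP, and neither is shown.

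Part of this stands: the article is not silent on which measure it calls primary. But the concern is not missing detail. The measure, the margin and the tests are all stated in the article, and they do not fit together. The AUC also comes last in the analysis plan, as an addition, with nothing to mark it as decisive.

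A reader might infer stronger things that the text does not support:

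- **That 0.73 can never apply to an AUC.** Dividing the area by its time span restores VAS points, and the article does not say that the area stays in point-hours.
- **That the pain grades leave some scores without a grade.** This needs scores recorded with decimals. The article gives no recording precision, and every whole-number score falls in a band.
- **That each test is repeated at every reading, multiplying the p-values.** The analysis plan does not say that testing is done by time point.

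**Conclusion.** The concern holds as a mismatch between stated items. The article gives no margin on the AUC's scale, no SD for it and no equivalence rule. It would be wrong to infer that the mean score is in better order: its margin is in the right units, but no listed analysis uses it. In addition, 0.73 is the difference observed in an earlier trial, and the article gives no clinical reason for treating it as an admissible difference.

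The size shows in the worked cases: the same data give 1.00 or 0.036 in one and 0.50 or 0.98 in the other, on opposite sides of 0.73. These rest on a trapezoidal AUC over 2 to 168 h and an unweighted four-reading mean. They show that the forms can disagree, not that they will in this trial.

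**What to change.** In Primary outcome variable and in Data processing and analysis plan:

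1. Name one decisive pain measure in VAS points, with its time window. The AUC divided by its time span would serve, but the window must be chosen deliberately, because over 2 to 168 h the 2 h and 4 h readings count for under 2%.
2. State a margin for that measure with its clinical justification, and an SD for that same measure. Rescaling the AUC does not by itself make 0.73 or 1.9 suitable.
3. Declare equivalence only if the confidence interval for the difference between arms lies wholly within the margin, and state its level.
4. Label the other mean scores and the grades as supportive.

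Record this as a dated amendment made before the final analysis. It should say that the interim analysis of 10 March 2022, planned to evaluate the primary outcome, came first, and that 45 of 58 patients were registered by 7 April 2022.

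No new data are needed. The cost is giving up several primary readings and disclosing a change made after an interim look. Writing the rule down will also expose a separate problem of precision: at 29 per arm with S = 1.9, a 95% interval has half-width 1.96 × 1.9 × √(2/29) = 0.98, already wider than 0.73.

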#### Secondary outcome variable

The mean operative time from anesthesia induction to the end of open hemorrhoidectomy will be recorded in both groups.

#### Tertiary outcome variable

The tertiary outcome is the cost-effectiveness of the 2 surgical approaches in relation to the amount of materials used in the 2 arms.

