Open hemorrhoidectomy in most low- and middle-income countries (LMICs) is performed under saddle block which requires a trained anesthetic provider and is associated with delays in the initiation of surgery, postoperative urinary retention, neural injury, direct nerve and spinal cord injury, cauda equina syndrome, epidural hematoma post-dural puncture headache, failed block, epidural abscess, and hematoma [2, 12, 13]. These complications increase the duration of hospital stay and morbidity [13]. The few numbers of anesthetic providers in developing countries like Uganda (0.05 per 100,000 population compared to 17.85 per 100,000 in the UK [14]) have been seen as a hindrance to access and performance of open hemorrhoidectomy especially at low-level facilities despite open hemorrhoidectomy being a very common surgical procedure [8]. The costs of anesthetic procedures have become an important factor in the selection of the best technique for benign anal surgeries [10]. Saddle block needs a trained anesthetist to administer the anesthesia in order to perform open hemorrhoidectomy and has been associated with a long hospital stay [2, 13] which increases the cost related to OH compared to OH done under local anesthesia [2, 3, 9, 10].

While open hemorrhoidectomy under local anesthesia has been shown to have lower complication rates and more cost-effective by saving anesthetics for other surgeries, it has been also found to increase patient turnover because of the shorter operative time [2, 7]. In spite of these benefits, LA is still not considered as a first-line technique in low-income countries like Uganda. To explore the applicability of LA for OH in a limited setting, a well-designed randomized controlled trial is needed.

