## Specific objectives

The following are the specific objectives:i.To compare the occurrence of postoperative pain following open hemorrhoidectomy under local anesthesia versus open hemorrhoidectomy under saddle blockii.To compare the mean operative time for open hemorrhoidectomy under local anesthesia versus open hemorrhoidectomy under saddle blockiii.To compare the cost-effectiveness between open hemorrhoidectomy under local anesthesia and saddle block

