## Discussion

### Study strengths

Open hemorrhoidectomy under local anesthesia has the potential to offer benefits to patients including expediting return to baseline and functional status, shorter hospital stay by meeting the discharge criteria faster, reduction in costs because of reduced length of stay, and reducing complications. The postoperative occurrence of pain, the main operative time, and cost-effectiveness will be assessed and reported for the first 7 days. This study is a randomized clinical trial that will provide level 1 evidence for evidence-based clinical practice about short-term surgical outcomes in open hemorrhoidectomy using an affordable alternative of low-cost technique in LMICs.

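### The third objective promises cost-effectiveness, but the outcome and its assigned analysis support at most a comparison of material cost

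*Protocol article*

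**What the plan says.** Under Specific objectives, the third aim is "To compare the cost-effectiveness between open hemorrhoidectomy under local anesthesia and saddle block". Under Tertiary outcome variable, that aim becomes cost-effectiveness "in relation to the amount of materials used in the 2 arms".

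Under Data processing and analysis plan, the one sentence that mentions this outcome reads: "Cross tabulation will be performed between the two open hemorrhoidectomy techniques for categorical cost-effective analysis". The sentence after it provides for a two-tailed t-test on a difference in means but does not say of which variable.

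Under Study limitations, a price source, a Ugandan medical store, is given for materials: "No similarity in the price of materials used during the study will be settled by the use of prices from the Joint Medical Store of" (quote cut short here).

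The rationale locates the savings elsewhere. The Introduction says that saddle block needs a trained anesthetist and "has been associated with a long hospital stay", and presents both as raising its cost. It adds that complications prolong stay, and that shorter operations under local anesthesia raise patient turnover. Study strengths anticipates "reduction in costs because of reduced length of stay", and the abstract's discussion adds complications as a source of savings.

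**The concern.** A cost-effectiveness result needs a cost for each arm, an effect for each arm, and a link between the two. The article names one cost component, materials, and no effect to set against it. The components on which the rationale rests are outside the outcome.

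The assigned analysis also suits the quantity poorly. Material cost per patient is a continuous amount, and a decision-maker needs the difference in its mean. A table of categories does not give that difference, and its result depends on where the category limits are set.

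At stake is the wording of one of three specific objectives, which is repeated in the abstract. Study rationale says that knowledge of cheaper surgical options is needed to inform policy in a low-income setting. A statement on cost-effectiveness drawn from consumables alone would be read as covering staff and bed use, which it would not.

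**Working it through.** The document gives no cost figure, so there is nothing to reproduce or recompute. The check sets its passages side by side.

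**Step 1. Cost components in the rationale against the outcome as defined.**

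| Component | Where the protocol raises it | In the tertiary outcome? | Listed as a study variable? |
|---|---|---|---|
| Materials | Tertiary outcome variable; Study limitations (price source) | Yes | Yes |
| Trained anesthetic provider | Introduction | No | No |
| Length of stay | Abstract; Introduction; Study strengths | No | No |
| Complications | Abstract; Introduction; Study strengths | No | No |
| Operative time | Introduction (turnover) | No | Yes, as the secondary outcome, not costed |

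The Introduction also mentions anesthetics saved for other surgeries. Drugs of that kind could be counted as materials. The other four components could not.

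**Step 2. Is cost linked to an effect?** Pain is the primary outcome and operative time the secondary one. Either could serve as an effect measure. No section joins either of them to cost.

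**Step 3. What analysis is fixed?** The only sentence that names the outcome assigns a categorical cross tabulation. The t-test sentence that follows fits operative time, for which means and standard deviations have just been mentioned, but could also cover cost. Read generously, it gives a comparison of mean material cost at standard prices. That is a legitimate cost comparison, but it is not cost-effectiveness.

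**Step 4. Which patients would be counted?** The intention-to-treat and per-protocol sets are named for the primary outcome only. A failed anesthetic technique appears among the Exclusion criteria and, under Interim analysis and Unblinding, as a ground for withdrawal. Trial discontinuation removes individual patients who convert from local anesthesia. Materials used in failed or converted blocks could therefore drop out of the arm that incurred them unless the plan says otherwise.

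**Step 5. Could the missing components still be added?** Operative time is recorded, with start and end points described in the study procedure. Discharge follows a score threshold, but time of discharge is not a listed variable, and neither is provider time. Trial status reports 45 of 58 patients registered by 7 April 2022 (45/58 = 77.6%), so items not collected from the start may be unrecoverable.

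**The case against.** The strongest defense has four parts.

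- **A cost comparison is already possible.** Materials are to be valued at one standard price list, and the unassigned t-test may be meant for mean cost. This stands. A reader might infer that the plan yields no valid cost comparison at all. The text does not support that; it leaves the matter ambiguous.
- **An article condenses.** The costing perspective, the category limits and any cost-effect ratio may be in a fuller document. This also stands, and their absence is not held against the plan. The definition in terms of materials and the categorical analysis are different, because the article states both. The outcome wording does not literally exclude other costs, but materials-only is its natural reading, and the price source agrees with it.
- **The omitted items may only reinforce the result.** On the protocol's own argument, provider need, stay and complications all favor local anesthesia. A reader might infer that full costing would reverse the result. Nothing shows this. Failed or converted blocks could count against local anesthesia, but the document gives no frequency or price for them.
- **The outcome is tertiary.** It does not drive the sample size or the pain conclusion. True, and this limits the reach of the point without removing it, since the aim is a stated specific objective.

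**Conclusion.** The point holds in limited form. As defined and analyzed in the article, the tertiary outcome cannot support a conclusion on cost-effectiveness: it covers materials, assigns a categorical table, and is tied to no effect. It can support a comparison of material cost if the plan says so and analyzes it as a continuous amount.

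The size cannot be estimated, because a price source is named but no prices or quantities are given. Neither the direction of any full-cost difference nor a reversal of it can be inferred.

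The conclusion assumes that the outcome means materials and not other costs, and that no fuller document redefines it. It does not depend on which variable the t-test is meant for. If that is cost, the comparison of means is already there, and only the label, the cross tabulation and the handling of failed blocks need correction.

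**What to change.** 1. Rename the third objective and the tertiary outcome as material cost per patient, valued at the Joint Medical Store prices already named.
2. Replace the cross tabulation with the between-arm difference in mean cost and its 95% confidence interval. A t-based or a bootstrap interval will serve. State that this is the cost analysis, so that the t-test sentence is no longer ambiguous.
3. Analyze by randomized arm, and include materials used in failed or converted blocks in the arm to which the patient was allocated.
4. Report the result as a material-cost comparison only, and make the abstract and discussion agree.
5. Optionally, cost the recorded operative time as a supplementary analysis with unit prices stated in advance of the comparison. Add provider time and hours to discharge only if they were actually recorded.

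Items 1 to 4 need a change of wording and a short analysis, with no new data provided that material use was also recorded for patients whose block failed or was converted. The downside is a narrower claim than the objective now makes. Item 5 requires unit prices for theater time, and should not be described as a full costing.
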